#### Informed Consent Form Or Information Sheet

In the informed consent form, patients will receive all the information about the study protocol, the confidential nature of personal data and will fill up a questionnaire before signing or refuse. There will be not inconveniences caused to the patients. No incentives are planned for the patients regarding the operation or the follow-up. All the medical informations obtained from the patients will be kept confidentially among the research scientists conducting the study. The patients will be free to withdraw from the study, whenever they want without any obligation.

### Ethical Approval

Approved by the ethical Committee of the Saint Orsola-Malpighi Hospital (see Additional files 1 and 2).

### Primary Endpoints

The aim of the study is to compare the results of early laparoscopic and laparotomic cholecystectomy for acute cholecystitis in terms of morbidity, mortality, conversion rate, operation time, hospital stay, postoperative pain, return to normal activity and aesthetic result.

The primary endpoints of our study will be:

To evaluate the value of laparoscopic cholecystectomy to reduce hospital stay

To evaluate the value of laparoscopic cholecystectomy to reduce postoperative pain

To evaluate the conversion rate

The onset of any other complications will be recorded intraoperatively, postoperatively, at discharge, at 7-days, 1-month and 6-months.

All the above mentioned data will be recorded in the Case Report Form and later stored in computer database. At the end of the study the final statistical examination will be carried out.

An interim statistical examination of the data will be done every 3 months during the period of patients' inclusion in the study. Then at the end of every completed follow-up period (1-month, 6-months).

The statistical analysis will be carried out using Epi Info 2000, Version 1.1 software package (Dean AG, Arner TG, Sangam S, Sunki GG, Friedman R, Lantinga M, Zubieta JC, Sullivan KM, Smith DC. Epi Info 2000, a database and statistics program for public health professionals for use on Windows 95, 98, NT, and 2000 computers; Centers for Disease Control and Prevention, Atlanta, Georgia, USA, 2000)

No incentives are planned for the patients regarding the operation or the follow-up.

The study will take approximately 6 months – 1 year for the inclusion period. According to the number of AC menaged monthly in all Centers, the duration of the inclusion period can be approximately of 1 year to reach the number of about 144 enrolled patients.

An interim report is planned at the end of any completed follow-up period.

AC is a common disease. Any improvement in this field will benefit many patients reducing morbidity, mortality, conversion rate, operation time, hospital stay, postoperative pain, return to normal activity and aesthetic result. All our patients will be informed about the study and an informed consent will be obtained. There will not be inconveniences caused to the patients. All the medical informations obtained from the patients will be kept confidentially among the research scientists conducting the study. The patients will be free to withdrawn from the study, whenever they want without any obligation.

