## Introduction

In the developmental stage of laparoscopic cholecystectomy it was considered 'unsafe' or 'technically difficult' to perform laparoscopic cholecystectomy for acute cholecystitis [1,2]. With increasing experience in laparoscopic surgery, a number of centers have reported on the use of laparoscopic cholecystectomy for acute cholecystitis, suggesting that it is technically feasible but at the expense of a high conversion rate, which can be up to 35 per cent [3,4] and common bile duct lesions [5].

Several randomized studies in the early 1980s had shown that performing early open cholecystectomy for acute cholecystitis was better than delayed cholecystectomy in terms of shorter hospital stay but both had similar operative morbidity and mortality rates [3]. Early surgery had since gained in popularity in the late 1980s [2]. Routine use of the open procedure might enable more patients to have the operations during the acute phase because most surgeons are practiced in this approach. The impact of hospital stay and morbidity must also be taken into account. There is the expectation that open operation is associated with more pain and longer hospital stay [6-8].

In some trials successful laparoscopic cholecystectomy during the period of acute inflammation is associated with an earlier recovery and shorter hospital stay when compared with open cholecystectomy [8]. Other studies did not confirm these results and the potential advantages of early laparoscopic cholecystectomy can be offset by a high conversion rate to open surgery [5]. Moreover in these studies a similar postoperative programme to optimize recovery comparing laparoscopic and open approaches was not standardized. Many studies also do not report all eligible patients and are not double blinded.

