### Statistics

Sample size has been calculated to reach a confidence level of 95% with a power of 80%.

A sample size of 144 patients is calculated supposing that the hospital stay for LC is shorter than 2 days. The sample size will be 72 patients for each group (144 patients for the whole study).

For comparison of the two groups, chi-square analysis and Fisher's exact test are used when appropriate for qualitative data, and the Student t-test (for normal variables) or the Mann Whitney U-test (for nonnormal variables) for quantitative data. For multivariate analysis the stepwise logistic regression is applied. A probability of 0.05 or less is accepted as statistically significant.

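### Three unranked primary endpoints share one 0.05 threshold, only hospital stay is sized, and conversion has no meaningful between-arm comparison

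*Protocol article*

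**What the plan says.** In the protocol article, the Primary Endpoints section gives three items in a plain list:

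- The first item concerns length of stay: "To evaluate the value of laparoscopic cholecystectomy to reduce hospital stay".
- The second item concerns pain: "To evaluate the value of laparoscopic cholecystectomy to reduce postoperative pain".
- The third item concerns conversion: "To evaluate the conversion rate".

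No order, split of alpha or rule for trial success goes with the list. The sentence before it says that the aim is to "compare the results of early laparoscopic and laparotomic cholecystectomy for acute cholecystitis in terms of morbidity, mortality, conversion rate" and several further outcomes.

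The Statistics section derives 144 patients, 72 per group, from an assumption about hospital stay. It gives no effect size for pain or conversion. It then offers a menu of tests for comparing the two groups, including "chi-square analysis and Fisher's exact test are used when appropriate for qualitative data", and one rule for all of them: "A probability of 0.05 or less is accepted as statistically significant".

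The Data Collection section records pain by VAS at rest and on coughing, at return to the ward and at 12 and 24 hours. It says that parenteral and oral analgesic requirements will also be analysed as a measure of pain. None of these is named as the primary pain measure.

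The Introduction shows what conversion means: the advantages of laparoscopic surgery "can be offset by a high conversion rate to open surgery".

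**The concern.** There are two faults in how the primary endpoints are fixed.

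First, stay and pain are both comparative, both primary and both subject to the same threshold. Nothing says whether one, the other or both must succeed. If either suffices, the chance of a false positive trial exceeds the nominal 5%. Pain adds to this because it is itself a set of measures. The sample size gives assurance for stay only.

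Second, conversion is by definition a change from laparoscopic to open surgery, so it is zero by design in the open arm. Listing it among the results to compare invites a test of whether the laparoscopic conversion rate equals a value that cannot be other than zero. Rejecting that hypothesis says nothing about which operation serves patients better, yet it would carry the label of a primary result.

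**Working it through.** **Inputs.** From Statistics: 72 per arm, threshold 0.05, 80% power. From Primary Endpoints: two comparative primaries plus conversion. From Data Collection: 2 VAS conditions × 3 times = 6 scores, plus 2 kinds of analgesic use, so 8 pain measures. From the Introduction: conversion of up to 35%. Assumed: two-sided tests.

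**1. The plan's own figure.** The 144 cannot be reproduced, because no SD is stated and the two-day wording is ambiguous. Read as a 2-day difference (an assumption), n per arm = 2·SD²·(1.960 + 0.842)²/2². Setting n = 72 gives SD = 2·√36/2.802 = 4.28 days, a standardised difference of 0.467. So 72 per arm can be matched to hospital stay, but only with an SD solved backwards. Nothing comparable can be attempted for pain or conversion.

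**2. Family-wise error, stay and pain.** Assume that either significant result counts as success and that there is no true difference on either.

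- Independent tests: 1 − 0.95² = 0.0975.
- Correlation 0.5 between the test statistics: 0.091.
- Upper bound: 0.05 + 0.05 = 0.10.

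This gives about 9–10%. Conversion is left out because it has no valid between-arm null.

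**3. Pain as a family.** Assume that all 8 measures are tested separately at 0.05, with a common correlation between them.

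| Correlation | Chance of at least one false positive |
|---|---|
| 0 | 1 − 0.95⁸ = 0.34 |
| 0.5 | 0.25 |
| 0.7 | 0.19 |
| 0.9 | 0.12 |

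**4. Conversion against a structural zero.** With x conversions in the laparoscopic arm and none in the open arm, the two-sided Fisher p-value is 2·C(72, x)/C(144, x).

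- x = 5 (6.9%): p = 0.058.
- x = 6 (8.3%): p = 0.028.

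So six conversions are enough. P(X ≥ 6) for a binomial with n = 72:

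| True conversion rate | Probability of p ≤ 0.05 |
|---|---|
| 10% | 0.738 |
| 20% | 0.998 |
| 35% | > 0.999 |

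**5. Conversion as a one-arm estimate.** The approximate 95% half-width is 1.96·√(p(1 − p)/72): 0.092 at 20% and 0.110 at 35%. Exact intervals are slightly wider: 14/72 gives 11.1% to 30.5%, and 25/72 gives 23.9% to 46.9%.

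**6. The alternative of splitting alpha.** With a 2-day difference and SD 4.28, testing stay at 0.025 needs 2·4.28²·(2.241 + 0.842)²/4, which rounds up to 88 per arm (176 in total). Keeping 72 per arm leaves Φ(2.802 − 2.241) = 71% power for stay.

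**The case against.** The strongest reply is that the multiplicity method, the order of tests and the exact pain summary commonly sit in an analysis plan, and this is a condensed article. That stands as far as it goes: their absence alone would be no finding. But which endpoints are primary, which one is sized and what threshold applies are all stated here. The fault lies in that structure.

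Second, the article assigns no alpha to any endpoint and states no success rule. A reader might infer that three endpoints are each formally tested at 0.05 and that any one wins the trial. The text does not say so. The inflation in step 2 is conditional on an either-one rule. If both comparative primaries had to succeed, alpha would not inflate. Power would then be the issue, since only stay is sized. Sizing on one of several primaries is not in itself an error.

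Third, the conversion item is worded differently from the other two. It names no contrast between arms and can be read as a single-arm estimate, and the test menu is generic. A reader might infer a planned chi-square or Fisher test of conversion that must come out significant. Neither part is supported. No test is assigned to conversion, and at a true rate of 10% the Fisher result would miss significance about 26% of the time (1 − 0.738). What remains is that the aim sentence places conversion among the results to compare, so the section has to be reconciled.

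Fourth, no section says that the eight pain measures are tested separately. A summary or repeated-measures analysis is not excluded, and the correlations are chosen, so step 3 is illustrative only.

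**Conclusion.** The concern holds in a limited form. The article fixes three unranked primaries, sizes one, applies a single threshold to everything, and includes in its stated comparison an outcome that can occur in one arm only.

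The figure that follows most directly from the listed endpoints is a family-wise error of about 9–10% for stay and pain, given two-sided tests and an either-one success rule. The range of about 12–34% for pain further assumes eight separate tests with correlations from 0.9 down to 0.

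A between-arm test of conversion would be uninformative whatever its p-value. Significance is likely (74% at a true rate of 10%, 99.8% at 20%) but not guaranteed. Hospital stay is unaffected by this multiplicity if it alone carries the primary test at 0.05.

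**What to change.** - Name hospital stay, the endpoint that was sized, as the single primary endpoint, tested at 0.05.
- Name one pain measure in advance as the next endpoint in a fixed sequence, tested at 0.05 only if stay is significant. Which measure is for the sponsor to choose. Treat the remaining pain measures and other outcomes as descriptive.
- Take conversion out of the between-arm comparisons, in both the aim sentence and the endpoint list. Report it in the laparoscopic arm only, as a proportion with an exact 95% confidence interval and no p-value. Precision is about ±9 points at 20% and ±11 at 35% by the normal approximation, and slightly wider for the exact interval.

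The cost is a few sentences, but they demote two stated primaries, so this is a protocol amendment and should be made before outcome data are compared. The sample size stays at 144. The downside is that no confirmatory pain claim is possible if stay is not significant. If the sponsor wants pain to stay primary, splitting alpha equally is also valid. Under the assumptions in step 6 it needs about 176 patients, or accepts 71% power for stay at 144.

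### If significance may be claimed at any three-monthly examination, the single 0.05 threshold gives a false-positive rate of about 8% to 13% for hospital stay or pain, not 5%

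*Protocol article*

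**What the plan says.** Four statements in the protocol article bear on this point.

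- **Schedule of looks (Primary Endpoints):** "An interim statistical examination of the data will be done every 3 months", for as long as inclusion runs. Further examinations follow at 1 month and 6 months of follow-up, and a final one closes the study. The same section adds: "An interim report is planned at the end of any completed follow-up period". Interim and final analyses are both called a statistical examination.
- **Length of inclusion (Primary Endpoints):** "The study will take approximately 6 months – 1 year for the inclusion period". The section then expects about one year to reach roughly 144 patients.
- **Threshold (Statistics):** after listing the tests for comparing the two groups, the section says: "A probability of 0.05 or less is accepted as statistically significant". No other level appears for any analysis.
- **Error level (Statistics):** "Sample size has been calculated to reach a confidence level of 95% with a power of 80" per cent.

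The article does not describe the interim examinations as descriptive, pooled or limited to safety. Nor does it say that a claim may be made, or the trial stopped, on the strength of one.

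**The concern.** A 5% error level belongs to one test. The article sets a calendar of repeated statistical examinations and supplies a single threshold. A reader who applies the text literally would test the accumulating data at 0.05 each quarter and could declare a difference the first time p fell to that level.

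The two comparative primary endpoints are fully exposed to this. Under Data Collection, pain is scored on return to the ward and at 12 and 24 hours, and hospital stay is known at discharge. Each quarterly dataset therefore holds final values for nearly everyone operated on so far.

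At stake is whether a reported difference in stay or pain carries the 5% risk of a false claim that the sample size paragraph implies, or a risk of up to about two and a half times that (12.6 / 5 = 2.5).

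**Working it through.** **Inputs from the article**

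- Nominal level 0.05 at every test (Statistics). Sidedness is not stated; I assume two-sided, so the critical value is 1.96.
- 144 patients, 72 per group (Statistics).
- One look every 3 months over 6 to 12 months (Primary Endpoints): 6/3 = 2 looks, 12/3 = 4 looks, with the last at the end of inclusion.

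**The plan's own figure.** The article bases 144 on "supposing that the hospital stay for LC is shorter than 2 days". It gives no standard deviation, so the figure cannot be reproduced. Read as a 2-day difference, 72 per group with 80% power implies

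SD = 2 / [(1.960 + 0.842) × √(2/72)] = 2 / (2.802 × 0.1667) = about 4.28 days.

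This is a single-test calculation. Nothing below depends on it.

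**Error with repeated looks.** Let t_k be the fraction of the final information at look k, and Z_k the standardised between-group statistic. Under the null hypothesis corr(Z_j, Z_k) = √(t_j/t_k) for j < k, and

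error = 1 − P(|Z_1| ≤ 1.96, …, |Z_K| ≤ 1.96).

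With even accrual, 2 looks add 144/2 = 72 patients each and 4 looks add 144/4 = 36 each. Recursive numerical integration gives:

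| Equally spaced looks at 0.05 | Overall two-sided error |
|---|---|
| 1 | 5.0% |
| 2 (6-month inclusion) | 8.3% |
| 3 | 10.7% |
| 4 (12-month inclusion) | 12.6% |

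One look returns the nominal 5%, which checks the method. A simulation of 1,000,000 trials gives the same values.

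**Sensitivity to spacing**

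- A separate final test soon after the last quarterly look: 8.9% for information fractions 0.5, 0.97, 1; 13.0% for 0.25, 0.5, 0.75, 0.98, 1.
- Slow early accrual, 0.15, 0.4, 0.7, 1: 13.6%.

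**The 1-month and 6-month examinations.** By then stay and early pain are complete, so retesting them adds almost no new information. I have not counted these as further looks.

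**After the fix**

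- One final test only: 5.0%.
- p<0.001 at three interims and 0.05 at the end: about 5.1%. Simple addition caps it at 0.05 + 3 × 0.001 = 5.3%.
- For comparison, a constant level that holds 5% overall (Pocock) is 0.0294 for 2 looks and 0.0182 for 4, which would also tighten the final test.

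**The case against.** The strongest reply is that the article never says a hypothesis test of the primary endpoints will be run at an interim, or that a positive result could be declared there. It fixes 144 patients, contains no stopping provision and names a final examination. If the conclusion comes only from that final analysis, the error is 5%. This stands, and it makes the point conditional. A reader might infer that the plan's error rate simply is 8% to 13%; the text does not establish that.

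A second reply is that this is a condensed article and that interim boundaries usually sit in a full protocol or SAP that is not shown. That is fair for the detail of a boundary. But the article itself states both the calendar of looks and the only threshold, and together they do not hold 5% unless the interims are barred from making a claim. That is a rule badly fixed, not merely a detail left out.

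Three stronger readings are also tempting and do not hold.

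- **All three primary endpoints are affected.** Conversion can occur only in the laparoscopic arm, so it has no between-group test and no such error to inflate.
- **Interim results will reach the surgeons who decide discharge.** No section says who sees them. Data Collection gives postoperative care and discharge to a second team blinded to the approach.
- **Looks and endpoints can be compounded into one larger figure.** Having more than one primary endpoint is a separate question, and the correlation between stay and pain is not given.

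**Conclusion.** The concern holds in conditional form. As written, the three-monthly schedule and the lone 0.05 threshold leave open a use of the interims under which the stated 95% confidence is not delivered. For hospital stay and for postoperative pain, each taken separately, the two-sided false-positive rate would be about 8.3% with 2 looks and 12.6% with 4. The article's own expectation of about one year points to the upper end.

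These figures assume two-sided tests, equally spaced looks, complete stay and pain data at each look, and that significance may be claimed at any of them. The spacing assumption matters little: the variants tried run from 8.9% to 13.6%. The last assumption decides the matter. If the interim examinations are descriptive only, the rate is 5% and all that is missing is a sentence saying so.

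**What to change.** Add to the Statistics section, before the first quarterly examination, one of the following:

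1. **Preferred.** No interim examination tests hospital stay or postoperative pain between arms for significance; each of these endpoints gets one final test at 0.05.
2. **If an early efficacy look is wanted.** Require p<0.001 at each interim (Haybittle-Peto) and keep 0.05 for the final test.

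Under either option, state that the 1-month and 6-month reports do not retest stay and early pain. By-arm review of safety may continue, since limiting it to pooled data would remove the comparison of harms between the two operations. Its results should be kept from the surgeons who recruit and treat.

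The cost is one or two sentences and no extra patients. The downside is almost no chance of an early efficacy claim: none under the first option, and only for an extreme difference under the second.
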